### Missing data

The possibility of loss to follow-up has been considered and will be calculated as a part of the sample size estimation. The dropout rates and reason will be recorded. In addition, we will account for other types of randomly missing data by treating dropouts as non-success or non-survival using the intention-to-treat principle.

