### Criteria

The inclusion criteria are as follows: meet the 2018 China College of Dermatology diagnostic criteria for plaque psoriasis; skin lesions involve ≤ 10% BSA (the lesions are mainly located on the torso/limbs, palm/sole, or face/scalp, with the vulva area being unaffected); aged 18–65 years; provide consent to participate in the study and sign the informed consent form.

The exclusion criteria are as follows: any clinically active skin diseases other than moderate to severe psoriasis vulgaris that might confound or influence the study aim; patients who received any systemic treatments within 4 weeks before the baseline visit; patients who received topical treatment within 2 weeks before the baseline visit (e.g., corticosteroids, ultraviolet light therapy including sunbathing); patients with an active infectious disease that is difficult to control; patients with a history of severe systemic disease, an alanine aminotransferase or aspartate transaminase level greater than 1.5-fold that of the average; any of the main routine blood indices (white blood cell count, red blood cell count, hemoglobin level, platelet count) lower than the normal limit, or other laboratory abnormalities; immunocompromised patients who may experience skin allergies or infection with moving cupping therapy; pregnant or lactating women; patients with a history of alcohol or drug abuse; and patients with a history of serious mental illness.

The exit/termination criteria were as follows: patient lost to follow-up; violation of the research plan (including lack of compliance [medication, contraindication, interview plan]); adverse events (including worsening of psoriasis above baseline [for example, PASI > 125%]) [27]; and pregnancy.

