### Safety monitoring

All participants will be advised to remain under supervision in the clinical research unit for 15 minutes after treatment. In addition, data of the participants will be monitored by the research team to detect any adverse events throughout the study, such as skin damage or potential allergies. All potential adverse events will be recorded. If any participant experiences an adverse effect due to trial participation, they will receive free treatment and compensation accordingly. If any concerns of the participants are identified during screening or clinical assessment, further clinical evaluations and/or investigations will be performed immediately. If concerns are identified during the study, the participants will be withdrawn.

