### Sample size

The sample size of the current trial was calculated based on the following formula [33]:
$$ {\mathrm{n}}_1={\mathrm{n}}_2=\frac{p_1\times \left(1-{p}_1\right)+{p}_2\times \left(1-{p}_2\right)}{{\left({p}_2-{p}_1\right)}^2}\times {\left({\mu}_{\alpha /2}+{\mu}_{\beta}\right)}^2 $$

According to recently published clinical trial results [27], the PASI-50 reached 62.1% (P_1_) in the study group and 35.3% in the control group (P_2_). Therefore, we assumed that the inspection level (α) was 0.05 and the power was 0.8 (β = 1-power = 0.2). For the two-sided tests, 51 participants will be required for each group. Given a 20% loss to follow-up, we expect to require 61 participants for each group. Therefore, this trial will require at least 122 participants.

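### Exit for non-compliance combined with failure scoring can turn measurable week-4 PASI outcomes into failures, and the sample size does not allow for that scoring

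*Protocol article*

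**What the plan says.** Four sections of the protocol article bear on this point.

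- **Criteria.** The exit/termination list contains "violation of the research plan (including lack of compliance [medication, contraindication, interview plan", next to loss to follow-up, adverse events (including worsening) and pregnancy.
- **Safety monitoring.** "If concerns are identified during the study, the participants will be withdrawn".
- **Missing data.** Loss to follow-up is said to be covered by the sample size. Other missing data are then handled "by treating dropouts as non-success or non-survival using the intention-to-treat principle".
- **Sample size.** The assumption is that "the PASI-50 reached 62.1% (P_1_) in the study group and 35.3% in the control group (P_2". From this, "For the two-sided tests, 51 participants will be required for each group", and then "Given a 20% loss to follow-up, we expect to require 61 participants for each group", so that "this trial will require at least 122 participants".

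The primary outcome (Primary parameters) is the proportion of patients whose PASI has fallen by at least 75% at 4 weeks. Table 1 schedules PASI at every visit, including week 4. No section says whether a participant who exits is still assessed.

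**The concern.** Non-compliance and plan violations happen after randomization, and most do not prevent PASI from being measured at week 4. The intention-to-treat principle, which the plan invokes, would keep such patients under assessment and use what is observed. Here the exit list removes them and the missing-data rule counts them as failures. The responder proportion then mixes skin response with administrative exit. If exit is unequal between arms, the comparison is biased: more exits on cupping work against cupping, and more exits on sham work in its favour.

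The second part is a mismatch between design and analysis. Adding 20% to the sample size replaces patients who leave the denominator. Under the failure rule they do not leave it. They stay and pull both response rates down, which shrinks the difference the trial is sized to detect.

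The word *non-survival* also has no referent, because no survival outcome is among the primary or secondary parameters.

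**Working it through.** **Inputs (Sample size section).** p1 = 0.621, p2 = 0.353 (both PASI-50 rates); two-sided α = 0.05; power 0.80; 51 per arm, raised to 61 for 20% loss. Allocation is 1:1 (Randomization, allocation, and blinding).

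**Step 1: reproduce the plan's figure.** The plan's formula is n = [p1(1−p1) + p2(1−p2)] / (p1−p2)² × (1.960 + 0.842)².

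- Numerator: 0.621 × 0.379 + 0.353 × 0.647 = 0.2354 + 0.2284 = 0.4638
- Denominator: 0.268² = 0.0718
- n = 6.457 × 7.849 = 50.68, rounded up to 51. The stated figure is reproduced.
- 51 × 1.2 = 61.2, written as 61. Dividing by 0.8 gives 63.75, that is 64.

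**Step 2: power formula on the same basis.** Power = Φ(|p1−p2| / √{[p1(1−p1) + p2(1−p2)]/n} − 1.960). At n = 51 with the stated rates this is Φ(0.268/0.0954 − 1.960) = 80.2%.

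**Step 3: apply the failure rule.** Suppose 20% exit in each arm, unrelated to response, and all are scored as failures.

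- Cupping: 0.8 × 0.621 = 0.497
- Sham: 0.8 × 0.353 = 0.282
- The difference falls from 26.8 to 21.4 points.
- Standard error at n = 61: √[(0.2500 + 0.2027)/61] = 0.0861
- Power = Φ(0.2144/0.0861 − 1.960) = Φ(0.529) = 70.2%. The pooled formula gives 68.4% and exact enumeration of the chi-square test 69.1%.

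**Step 4: vary the assumptions** (61 randomized per arm, plan's formula).

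| Assumption | Rates | Power |
|---|---|---|
| 20% leave the denominator (48.8 per arm remain) | 62.1% v 35.3% | 78.5% |
| 10% scored as failures | 55.9% v 31.8% | 79.0% |
| 15% scored as failures | 52.8% v 30.0% | 74.7% |
| 20% scored as failures | 49.7% v 28.2% | 70.2% |
| All exits are non-responders, or the cited rates already count dropouts as failures | 62.1% v 35.3% | 86.7% |

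Of the 10 points between 80.2% and 70.2%, 80.2 − 78.5 = 1.7 come from multiplying by 1.2 instead of dividing by 0.8. The other 78.5 − 70.2 = 8.3 come from failure scoring. With 64 per arm, power under failure scoring is 72.2%. Restoring 80% at 20% loss would take 77.3, that is 78 per arm (156 in total).

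**Step 5: unequal exit (an illustration; the documents give no exit rates by arm).** With no true effect, a 35.3% response in both arms, and exits of 20% on cupping and 10% on sham unrelated to response, the rule alone produces 0.8 × 0.353 − 0.9 × 0.353 = 28.2% − 31.8% = −3.5 points, against cupping. Reversing the exits gives +3.5 points.

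**The case against.** **Failure scoring is a recognised choice.** For a binary responder outcome, setting a missing value to non-response is common and often conservative. This stands. The fault is not the imputation itself, but that the exit rule can create missing values where a measurement could be had.

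**The loss of outcomes is inferred.** The article is silent on assessment after exit, and a fuller protocol might provide for it. This is fair. But the article does list non-compliance under exit/termination and does score dropouts as failures, so the natural reading of the text conflicts with its intention-to-treat label.

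**The missing-data text is ambiguous.** It first assigns loss to follow-up to the sample size and then speaks of other missing data, so it is arguable whether the 20% falls under the failure rule. The wording does call the affected patients dropouts, which makes that the natural reading, but it should be made explicit.

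**About 70% is one point in a range.** This stands. Multiplying both rates by 0.8 assumes that exits are equal between arms and unrelated to response. Patients who exit because of worsening would be PASI-75 failures anyway. The plan also does not say whether the cited rates are among evaluable patients.

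**Stronger readings that the documents do not support.** A reader might infer that the unblinded operating physician decides who counts as non-compliant. No section gives that role to the physician, and Data collection and management assigns data collection to a designated researcher and trained data collectors. A reader might also infer that local blisters will cause more exits on cupping. The background names blisters as the main adverse reaction, but no section makes them a specific exit trigger or gives exit rates by arm. Nor is the absence of a multiple-imputation analysis or of rules for the quantitative outcomes a fault here, since those are commonly left to the SAP.

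**Conclusion.** The concern holds in a limited form. As written, the Criteria, Safety monitoring and Missing data sections together allow measurable week-4 PASI outcomes to be counted as failures under an intention-to-treat label. The direction of any resulting bias depends on which arm has more exits, which the documents do not predict.

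The sample size does not match the failure rule at the plan's own loss rate. On the plan's rates, power at 61 per arm is about 69–70% for 20% loss, 75% for 15% and 79% for 10%. This rests on equal exits, exits unrelated to response, and cited rates taken among evaluable patients. If all exits are non-responders, or the cited rates already count dropouts as failures, power is about 87%.

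A reader might conclude that the trial has 70% power. The documents do not support that. The rates are for PASI-50 and the primary outcome is PASI-75, so neither 80% nor 70% is the power for the primary outcome, and that power cannot be computed from what is given.

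**What to change.** 1. Leave the clinical stopping criteria unchanged. Reconcile Criteria, Safety monitoring and Missing data by stating that stopping treatment, non-compliance or a plan violation does not end outcome assessment.
2. State that the scheduled week-4 PASI is still taken in these patients and analysed as observed in the randomized arm. Set only a truly missing week-4 PASI to non-response.
3. Delete *non-survival*.
4. In Sample size, restate the power as conditional on the failure rule: about 70% at 20% loss, with the range and assumptions above. Note that it rests on PASI-50 rates and is not the power for the PASI-75 primary outcome.

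A sensitivity analysis by multiple imputation from the weekly PASI is optional and can be left to the SAP.

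The cost is protocol wording, week-4 attendance by patients who have stopped treatment (a visit already in Table 1), and a less favourable stated power.

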### Ethics and dissemination

The study has been approved by the ethics committee of Yueyang Hospital of Integrated Traditional Chinese and Western Medicine (ref. approval no. 2019–003). Patients will be informed at the beginning of the study that they have the right to withdraw from the study at any time without providing a reason. Even in the event of a withdrawal, the required treatment will be provided to the patient. The results of the study will be published in an international peer-reviewed journal.

## Discussion

Psoriasis often requires multiple methods of combination therapy in the clinic; however, this does not always result in satisfactory outcomes. Therefore, there is increasing concern regarding the current combinations of CAM in modern medical practice. Cupping is a form of CAM that has existed for thousands of years in various civilizations. It plays a unique role in various diseases, including dermatology. Studies have found that cupping can lower the level of superoxide dismutase in the blood, which has a role in reducing oxidative stress [34, 35]. Cupping can also significantly reduce the hemoglobin level in the cupping area and increase the level of oxyhemoglobin. In addition, it can increase HSP-70 and β-endorphins to relieve pain [36]. Although the mechanism of moving cupping treatment for psoriasis is not clear, there are indications that moving cupping can alleviate plaque psoriatic skin inflammation and excessive thickening of skin lesions. Conventional treatment combined with moving cupping has a better curative effect. However, it is true that the therapeutic effect still requires further rigorous scientific verification.

Currently, only small-scale clinical research has been performed for moving cupping treatment of psoriasis. Relevant RCT studies did not adopt blinding methods, lacked placebo control, did not follow the CONSORT statement, and were published in languages other than English [26, 29]. Therefore, large RCTs are needed to assess the role and possible adverse outcomes of moving cupping for the treatment of plaque psoriasis.

This study will be the first placebo-controlled study of moving cupping for the treatment of plaque psoriasis with multiple centers, double-arm parallel groups, and a single-blind RCT. Furthermore, the study has several advantages. The first is that it will use a placebo control to exclude the placebo effect, reduce the risk of bias, and define the clinical efficacy of moving cupping for the treatment of plaque psoriasis. The second advantage is that, because of the large land area of China, the study will include a total of six hospitals in different regions, thus including various ethnic and socioeconomic populations. As such, its experimental design will increase the generalizability of the trial outcomes. However, this study also has some limitations. Due to the particularity of moving cupping therapy, it is difficult for different operators to maintain the same strength when moving the cup. Furthermore, because different cup sizes will be selected for the different treatment sites, adsorption forces will be inconsistent. All of these limitations may lead to the risk of bias. The placebo cupping therapy method has been used previously in only two clinical trials [37, 38]. Although the moving cupping placebo lacks absorption during treatment, we found that most patients do not understand the specific operation of the treatment method; therefore, they cannot distinguish between the moving cupping placebo and moving cupping. Patients were blinded to whether they are accepting real or placebo cupping. In conclusion, this study aims to verify whether moving cupping therapy is effective for treating plaque psoriasis. We also hope to provide a safe and effective treatment for plaque psoriasis through this study.

## Trial status

The protocol version number is 2.0 and the version date is May 15, 2019. The study plans to start recruiting participants in August 2019 and complete the recruitment in December 2020.

## Data Availability

We declare that the materials described in the manuscript, including all relevant raw data, will be freely available to any scientist wishing to use them for non-commercial purposes without breaching participant confidentiality.

## Abbreviations

BSA: Body surface area
CAM: Complementary and alternative medicine
DLQI: Dermatology Life Quality Index
DSMB: Data and Safety Monitoring Board
PASI: Psoriasis Area and Severity Index
PGA: Physician’s Global Assessment
RCT: Randomized controlled trial
TCMSSS: Traditional Chinese Medicine syndrome scoring scale
Th1: T-helper cell type 1
VAS: Visual analogue scale
